##### **Causality Assessment: Not Related**

The adverse event is clearly not related to the vaccine i.e. another cause of the event is most plausible; and/or a clinically plausible temporal sequence is inconsistent with the onset of the event and the vaccine administration; and/or a causal relationship is considered biologically implausible.

#### **8.4.6 Assessment of Expectedness of Adverse Event**

An unexpected AE is an AE, the nature or severity of which is not consistent with the applicable product (vaccine) information, e.g. investigator's brochure for an unapproved investigational product (vaccine), or package insert/summary of product characteristics for an approved product (vaccine). Assessment of expectedness of Adverse Event will be done by the Sponsor.

#### **8.4.7 Follow-up of Adverse Events and Assessment of Outcome**

The Investigator should follow-up a subject with an AE until the event has subsided / resolved or until the condition has stabilised. In addition, all serious adverse events and those non-serious events assessed by the Investigator as related to the investigational vaccine should continue to be

*Information contained in this publication is the property of EVI and ICGEB and is confidential and will not be disclosed to third parties without written authorization from EVI and ICGEB. No part of this document may be reproduced, stored in a retrieval system or transmitted in any form or by any means -electronic, mechanical, recording or otherwise - without the prior authorization of EVI and ICGEB*

[figure not shown][figure not shown]

followed even after the subject's participation in the clinical trial is over. Such events should be followed until they resolve or until the Investigator assesses them as "chronic" or "stable. Follow-up reports must be submitted to the Medical and Safety Monitor using SAE Report Form for serious adverse events or Data Clarification Request Form for non-serious events.

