**Primary Endpoint(s)**

The safety profile will be assessed on the basis of the following criteria

- Immediate reactogenicity (any event occurring within the first three (3) hours after each vaccination, with emphasis on allergic reactions)
- Local and systemic reactogenicity (any event occurring from three (3) hours post vaccination on Day 0 till Day 14 after each dose)
- Any unsolicited adverse events 28 days after each vaccination
- Any Serious Adverse Event (SAE) occurring from the first dose of vaccine till the last follow-up visit.
- Biological safety, 28 days after each vaccination, in reference with the baseline before the first dose, by measuring the following parameters:
  - Haematology: RBC Count, Haemoglobin\*, Haematocrit/Packed Cell Volume (PCV), MCV (Mean Corpuscular Volume), MCH (Mean Corpuscular Haemoglobin), MCHC (Mean Corpuscular Haemoglobin Concentration) on Days -14, 28, 56, 180, 208, 365
  - Platelet Count and Total Leukocyte Count (TLC) along with Differential Leukocyte Count (DLC) on Days -14, 28, 56, 180, 208, 365.  
\*If the haemoglobin drops below 13 gm/dL, then a direct Coomb's test and a peripheral blood smear/film will be prepared and examined for evidence of possible haemolysis
  - Serum Chemistry: Potassium, Sodium, AST, ALT, Direct, Indirect and Total Bilirubin, Alkaline Phosphatase, Gamma Glutamyl Transpeptidase (γGT), Creatinine, and Random blood glucose on Days -14, 28, 56, 180, 208, 365

The Investigator will be responsible for causality assessment i.e. assessment of the relationship of the AE to either of the assigned the study vaccines, using the following definitions: related or not related.

---

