## 4.6 Definition of Study Endpoints

### 4.6.1 Primary Endpoint(s)

The safety profile will be assessed on the basis of the following criteria

- Immediate reactogenicity (any event occurring within the first three (3) hours recorded every 30 minutes after each vaccination, with emphasis on allergic reactions)
- Local and systemic reactogenicity (solicited adverse events occurring from three (3) hours post-vaccination on Day 0 till Day 14 after each dose)
- Any unsolicited adverse events 28 days after each vaccination
- Any Serious Adverse Event (SAE) occurring from the first dose of vaccine till the last follow-up visit.
- Biological safety, 28 days after each vaccination, in reference with the baseline before the first dose, by measuring the following parameters:

- Haematology: RBC count, Haemoglobin\*, Haematocrit/Packed Cell Volume (PCV), MCV (Mean Corpuscular Volume), MCH (Mean Corpuscular Haemoglobin), MCHC (Mean Corpuscular Haemoglobin Concentration), Platelet Count and Total Leukocyte Count (TLC) along with Differential Leukocyte Count (DLC) on Days -14, 28, 56, 180, 208, 365.

\*If the haemoglobin drops below 13 gm/dL, then a direct Coomb's test and a peripheral blood smear/film will be prepared and examined for evidence of possible haemolysis.

- Serum Chemistry: Potassium, Sodium, AST, ALT, Direct, Indirect and Total Bilirubin, Alkaline Phosphatase, Gamma Glutamyl Transpeptidase ( $\gamma$ GT), Creatinine, and Random blood glucose on Days -14, 28, 56, 180, 208, 365.

The Investigator will be responsible for causality assessment i.e. assessment of the relationship of the AE to the assigned study vaccines, using the following definitions: related or not related.

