## 6 STUDY VACCINES

Two (2) vaccines will be used in the study, namely the investigational vaccine (JAIVAC-1 – Montanide ISA 720 malaria vaccine) and the control vaccine (Hepatitis B vaccine), both being referred together as the “study vaccines”. The vaccine under development, JAIVAC-1 malaria vaccine (PfMSP-119 and PfF2) will be referred to as the investigational vaccine; it has been developed by ICGEB and EVI and manufactured and supplied by Bharat Biotech International Ltd., Hyderabad, India. The quality control standards and requirements for the investigational vaccine as well as the adjuvant are described in separate release protocols and the required approvals for the clinical use of the investigational vaccine as well as the adjuvant will be obtained prior to start of the study.

The control vaccine used in this study is Gene Vac-B™ i.e. Recombinant Hepatitis-B Vaccine, I.P. and will be procured from Serum Institute of India Limited (SIIL), Pune, India and the respective prescribing information is provided in Package Insert provided with the vaccine (*Refer Appendix D*).

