## 8 SAFETY MONITORING

### 8.1 Introduction

The collection, recording, assessment and reporting of adverse events (AE) and serious adverse events (SAE) represent the core activities for the safety evaluation. These activities are under the direct responsibility of the Investigator.

The recording of adverse events is an important aspect of study documentation as the evaluation of the safety of three (3) intramuscular injections of the investigational vaccine (JAIVAC-1 – Montanide ISA 720 malaria vaccine) in comparison with that of the control vaccine (Hepatitis B vaccine) is the primary objective of this study. The procedure for evaluation of immediate reactogenicity, solicited adverse events and unsolicited adverse events is described Section 7. The investigator is responsible for the detection and documentation of events meeting the definition of an adverse event (AE) or a serious adverse event (SAE) as provided in Sections 8.4 and 8.5 of this protocol. This includes the evaluation of its seriousness, its severity, and the causal relationship to the investigational vaccine and/or concomitant therapy.

At each visit, the investigator will assess whether any AE including laboratory abnormalities has occurred. The investigator shall inquire for unsolicited AEs with non-suggestive questions to the subject at each study visit. The investigator shall attempt to establish a diagnosis of the event based on signs, symptoms and/or other clinical information. The diagnosis shall be recorded as the AE and/or SAE and not the individual symptoms.

If a laboratory abnormality or other abnormal assessment meets the definition of an AE or SAE, the Adverse Event or Serious Adverse Event Form shall be completed as appropriate. A diagnosis, if known or clinical signs and symptoms if diagnosis is unknown, rather than the laboratory abnormality shall be reported. If no diagnosis is known and clinical signs and symptoms are not present, then the abnormal finding shall be recorded. The subject shall be observed and monitored carefully until the AE resolves, the condition stabilises or its cause is identified completely. The investigator is responsible for ensuring that follow-up includes any supplemental investigations that may be indicated to elucidate the nature and/or the cause of the event.

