#### **8.4.5 Assessment of Causality of Adverse Events**

Assessment of causality Adverse Event (related or not related) will be done by the Investigator. The following scale will be used for rating the causal relationship of the AE to the investigational product (vaccine):

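### The product against which causality is judged differs between sections, so control-arm events may be rated inconsistently, and 8.4.7 words extended follow-up of non-serious events for the JAIVAC-1 arm only

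*Supplement*

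**What the plan says.** Section 6 sets the terms. It introduces JAIVAC-1 with Montanide ISA 720 and "the control vaccine (Hepatitis B vaccine), both being referred together as the" study vaccines. JAIVAC-1 alone "will be referred to as the investigational vaccine".

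The endpoint text covers both arms. Section 4.6.1 asks for "assessment of the relationship of the AE to the assigned study vaccines, using the following definitions: related or not related". The synopsis has "assessment of the relationship of the AE to either of the assigned the study vaccines".

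Section 8, which instructs the investigator, uses more than one reference. Section 8.1 lists "the causal relationship to the investigational vaccine and/or concomitant therapy" among the items to evaluate, and the lead-in to the scale in 8.4.5 speaks of "rating the causal relationship of the AE to the investigational product (vaccine"). Yet 8.4.2 refers to the study treatments, and 8.4.3 and 8.5.2 to the study vaccine.

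Section 8.4.7 has two follow-up sentences. The first covers any adverse event until it resolves or stabilises. The second adds follow-up after participation has ended for all serious events and for "those non-serious events assessed by the Investigator as related to the investigational vaccine should continue to be" followed.

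**The concern.** By the protocol's own definitions, *study vaccine* takes in the control and *investigational vaccine* does not. The trial is single-blind (4.5, 6.4.5, 11.1.3): investigators and assessors know which product each subject received. An investigator who applies 8.1 and the 8.4.5 lead-in literally knows that a Hepatitis B recipient has had no JAIVAC-1 and may enter *not related*. An investigator who works from 8.4.3 would judge the same event against the vaccine given and may enter *related*. No ambiguity of this kind arises in the JAIVAC-1 arm, so any resulting miscoding would fall on one arm only.

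This reaches the analysis. Comparing safety with the control vaccine is a primary objective (3.1), and 11.5.1.3 tabulates adverse events by causality and displays them by vaccine group. Fewer related events among controls could then reflect which section the rater followed. Read literally, 8.4.7 also gives explicit follow-up after participation to related non-serious events in one arm and not in the other.

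**Working it through.** No formula applies; the protocol states no figure that depends on this wording. The check is to set side by side every place that names the product against which causality is judged.

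| Place | Reference product | Covers control? |
|---|---|---|
| Synopsis, primary endpoints | assigned study vaccines | yes |
| 4.6.1 | assigned study vaccines | yes |
| 8.4.2 | study treatments | yes |
| 8.4.3, items recorded per event | study vaccine | yes |
| 8.5.2, serious events | study vaccine | yes |
| 8.1 | investigational vaccine, concomitant therapy | not named |
| 8.4.5, lead-in | investigational product (vaccine) | not as 8.4.6 uses the phrase |
| 8.4.7, second sentence | investigational vaccine | no |
| 8.4.5, *Related* and *Not Related* definitions | the vaccine | neutral |

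Five places cover both arms, three point to JAIVAC-1, and the two category definitions are neutral.

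**Could the narrow terms be loose synonyms?** The surrounding text suggests not. Section 8.1 contrasts the investigational vaccine, named as JAIVAC-1, with the control in the same paragraph. Section 8.4.6 sets an unapproved investigational product against an approved product. Section 8.5.4 pairs the investigational vaccine with the Investigator's Brochure and the control with its package insert. Section 8.5.4 also sends the causality rating of serious events back to 8.4.5, so the lead-in there matters for those too.

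**Which analyses depend on the rating?**
- 11.5.1.2, solicited reactions: proportions by vaccine group with no causality filter, so unaffected.
- 11.5.1.3, overall and by severity: unaffected.
- 11.5.1.3, by causality: exposed.

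**Who is exposed?** The control recipients: 3 cohorts × 5 = 15 of 45, or 33%.

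**How wide is the follow-up gap?** Under 8.4.2 adverse events are reported until 28 days after each dose, so the last window closes at 180 + 28 = Day 208. Participation runs to Day 365, and 365 − 208 = 157 days. For a subject who completes the study, only a related, non-serious control event still unresolved and not stabilised about 157 days or more after that window closes would come under the arm-specific clause. For a subject who leaves early (5.4.4) the interval can be shorter.

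**The case against.** The strongest reply is that section 8 as a whole does provide for related events in the control arm. Section 8.4.3 lists what is documented for each event, and there the item is the relationship to the study vaccine. The category definitions say only *the vaccine*. Section 8.5.4 checks the expectedness of serious control-arm events against the package insert, so those events go through the same assessment. This stands. A reader might infer from 8.1 and 8.4.5 that a control event can never be rated related, so that the control arm shows no related events by construction. The documents do not support that inference; they support only a risk of inconsistent rating.

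On follow-up, the first sentence of 8.4.7 and the matching text in 8.1 cover every event in either arm until it resolves or stabilises, with no stated cut-off at study end, and all serious events in both arms are named in the second sentence. This also stands, so it would be wrong to say that control events as a class lose follow-up. It does not remove the point. The second sentence opens as an addition to the first and speaks expressly of the time after participation. It would add little if the first already ran that far, so the two need reconciling.

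Finally, 11.5.1 makes the analysis descriptive and disclaims comparison between groups. That lowers the stakes, but readers will still look at a causality table laid out by vaccine group, and 3.1 makes the comparison with control a primary objective.

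**Conclusion.** The contradiction is real and lies in operative safety text. It is modest in reach: one breakdown in 11.5.1.3, for 15 of 45 subjects, plus one clause in 8.4.7 that affects probably few non-serious control events.

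The effect on the related-event rate cannot be put in figures from these documents. An estimate would need an assumed rate of control-arm reactions, and it would have to suppose that the narrow reading is used throughout, which 8.4.3 and the category definitions contradict. It is therefore best reported as a risk of inconsistent coding with no percentage attached.

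The conclusion assumes that the section 6 definitions govern the later sections and that no CRF instruction outside these documents already fixes the reference product. The change is worth making because it bears on a primary-objective comparison and costs almost nothing.

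**What to change.** In 8.1 and in the lead-in to 8.4.5, name the assigned study vaccine (investigational or control) as the reference for causality, in line with the synopsis, 4.6.1, 8.4.2, 8.4.3 and 8.5.2. Use the same term on the CRF and the SAE Report Form.

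In 8.4.7, reconcile the two sentences with each other and with 8.1, so that the follow-up wording does not differ by arm. How long such events are followed is for the sponsor and the investigator to settle.

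The cost is three wording changes and possibly the follow-up of a few control-arm events. Sample size, visits and analysis methods are unchanged. If rating has already begun, control-arm entries marked *not related* should be queried to establish which reference product was used.

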## 8.5 Serious Adverse Events

### 8.5.1 Definition of a Serious Adverse Event

Serious Adverse Event (SAE) is defined as any untoward medical occurrence that at any dose:

- results in death,
- is life-threatening,
- requires subject hospitalisation or prolongation of existing hospitalisation,
- results in persistent or significant disability/incapacity, or
- is a congenital anomaly/birth defect

(ICH GCP definition)

**Life threatening AE:** An AE is life threatening if the subject was at immediate risk of death from the event as it occurred; i.e. it does not include a reaction that if it had occurred in a more serious form it might have caused death. For example, drug-induced hepatitis that resolves without evidence of hepatic failure would not be considered life threatening even though drug-induced hepatitis could be fatal.

**Hospitalisation:** In general, hospitalisation signifies that the subject has been detained at the hospital or emergency ward (usually involving at least an overnight stay) for observation and/or treatment that would not have been appropriate in the physician's office or out-subject setting. When in doubt as to whether hospitalisation' occurred or was necessary, the AE should be considered serious. Hospitalisation for elective surgery or routine clinical procedures that are not the result of an AE (e.g., elective surgery for a pre-existing condition) need not be considered AEs. If anything untoward is reported during the procedure, that occurrence must be reported as an AE, either 'serious' or 'nonserious' according to the usual criteria.

**Disabling/incapacitating AE:** An AE is incapacitating or disabling if it results in a substantial and/or permanent disruption of the subject's ability to carry out normal every-day activities.

**Medically important condition:** Medical and scientific judgment should be exercised in deciding whether expedited reporting is appropriate in other situations, such as important medical events that may not be immediately life-threatening or result in death or hospitalisation, but may jeopardise the subject or may require intervention to prevent one of the other outcomes listed in the definition above. These should also usually be considered serious. Examples of such events are intensive treatment in an emergency room or at home for allergic bronchospasm, blood dyscrasias or convulsions that do not result in hospitalisation, or development of drug dependency or drug abuse.

### 8.5.2 Reporting Serious Adverse Events

To ensure subject safety, every SAE, regardless of suspected causality, occurring after the subject has received the first dose of the vaccine till Day 365 (end of study) must be reported by the Principal Investigator/designee to the Sponsor and DLS within 24 hours of the knowledge of its occurrence. Recurrent episodes, complications, or progression of the initial SAE must be reported as follow-up to the original episode, regardless of when the event occurs. This report must be submitted within 24 hours of the investigator receiving the follow-up information. An SAE that is considered completely unrelated to a previously reported one should be reported separately as a new event.

Every SAE will be reported to the Medical and Safety Monitor at DLS as well as the Sponsor Representatives (both ICGEB and EVI) by telephone/e-mail within 24 hours from observation, regardless of the treatment group or suspected relationship to study vaccines. In addition, for each SAE, the investigator must assess the relationship to the study vaccine, complete the SAE Report Form and send the completed, signed form by e-mail/fax as soon as possible. The telephone and fax number of the Medical and Safety Monitor at DLS will be listed in the investigator folder provided to the study site. The original copy of the SAE Report Form and the fax confirmation sheet must be kept with the case report form documentation at the study site. The initial report should be followed by a full written summary (using SAE Report Form) detailing relevant aspects of the AE, in sufficient detail to allow for a complete medical assessment of the case and independent determination of possible causality. In general, this information includes copies of relevant hospital case records, autopsy reports and other documents where applicable. The initial and follow-up reports shall identify the trial subjects by the unique randomisation number assigned to each subject.

### 8.5.3 Processing and Regulatory Submission of SAE Reports

All SAE reports will be processed, evaluated and reported to the Sponsor, IEC(s)/IRB(s) and regulatory agencies as per applicable timelines.

Every serious adverse event must be reported by the Investigator to the Medical and Safety Monitor, DLS and the Sponsor representatives (ICGEB/EVI) within 24 hours of the knowledge of SAE.

The Medical and Safety Monitor will send the following to the Sponsor's Contact Person; preferably by e-mail or fax:

- Reports for death or life-threatening SAEs not later than one (1) business day from Date of Receipt from the Investigator
- Reports for other SAEs not later than two (2) business days from the Date of Receipt from the Investigator
- Reports on pregnancy cases in female partner of male subjects (Pregnancy Reports), as applicable not later than two (2) business days from the Date of Receipt from the Investigator

*Information contained in this publication is the property of EVI and ICGEB and is confidential and will not be disclosed to third parties without written authorization from EVI and ICGEB. No part of this document may be reproduced, stored in a retrieval system or transmitted in any form or by any means -electronic, mechanical, recording or otherwise - without the prior authorization of EVI and ICGEB*

[figure not shown][figure not shown]

In addition, the following SAE Reporting timelines will be followed:

- The Principal Investigator will send the SAE report to the site EC within 7 working days from the day of awareness of occurrence of the SAE
- The ICGEB Representative will send the SAE report to the ICGEB IRB within 7 working days from the day of awareness of occurrence of the SAE
- DLS will send the SAE Reports for unexpected and related SAEs, which are deaths/life-threatening SAEs occurring at study site to the DCGI within 7 calendar days from the day of awareness of occurrence of the SAE with a follow-up report sent within the next 8 calendar days.
- DLS will send the SAE Reports for all other SAEs occurring at study site to the DCGI within 14 calendar days from the day of awareness of occurrence of the SAE

